### Statistical Analysis

We will analyze differences in the cardiovascular risk profile, BMD, and neurocognitive functioning between the early RRSO group and the late/non-RRSO group using multivariable linear regression analyses and logistic regression analyses with clinically relevant cutoff points for the outcomes of interest. The analyses will be adjusted for confounders, including lifestyle, reproductive factors, and medication use, where applicable. For the analysis of patient-reported outcomes, such as HRQoL, sexual functioning, and menopausal symptoms, we will use mixed effect models.

We expect approximately 40% of the women to have a breast cancer history and will perform the analyses separately in women with and those without a breast cancer history, as breast cancer treatment may affect outcomes. Additional subgroup analyses will be performed according to HRT use (yes/no), *BRCA1/2* mutation status, age at RRSO (<40 years/≥40 years), and time since RRSO (10-15 years/>15 years).

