### Sample Size Calculation

We based our sample size calculations for cardiovascular status on subclinical atherosclerosis by assessing the differences in the CAC score between women in the early RRSO group and women in the late/non-RRSO group. We chose a clinically relevant cutoff for the CAC score of 100 Agatston units (AU). According to the MESA trial, 10% of subjects between 55 and 65 years of age exceed this value [78]. For sample size estimation, we hypothesized that 20% of the early RRSO group exceeds this value of 100 AU. In logistic regression with an elevated CAC score (>100) as the outcome and with 250 women in the late/non-RRSO group and 500 women in the early RRSO group, we have 80% power to detect an odds ratio of 1.9 at an α value of 5%.

With 750 women in our study, we will be able to detect a difference of 0.07 g/cm^2^ in BMD between the early RRSO and late/non-RRSO groups, as observed between women with premature and normal menopause and assuming an SD of 0.15 [79]. Statistical power for analysis of cognitive functioning is based on a previous neuropsychological study on the effects of oophorectomy on cognitive impairment and dementia [34]. This study reports relevant differences in 427 women with bilateral oophorectomy before the age of 49 years, compared to age-matched women without oophorectomy, with a median follow‐up of 25 years. As our neurocognitive tests are more sensitive than the tests screening for dementia, we expect to be able to detect smaller differences in cognitive functioning and distinguish between different cognitive domains, and with 750 participants, we have 90% power to detect an effect size of 0.25 with a *P* value set at .05 (two tailed). To detect a relevant difference between groups for the various HRQoL measures, we will use a half SD (an effect size of 0.5) to define clinically relevant group differences (over time). This requires about 67 patients per group. The available sample will be more than adequate to conduct subgroup analyses as well.

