One of the major strengths of our study is that it will be the first to examine the health effects of premenopausal RRSO at less than 45 years with a follow-up of over 10 years compared to controls with natural menopause. Additionally, owing to the large number of participants, we will have sufficient power for subgroup analyses. A limitation of our study could be survivor bias. Owing to the inclusion criterion of at least 10 years of follow-up, patients may already have died of relevant study outcomes before study inclusion. However, as we conduct the cross-sectional study within a well-characterized cohort, we can assess the extent of such bias by collecting cause of death information for potentially eligible but already deceased women.

This initial cross-sectional study will provide prevalence rates of noncancer outcomes. Therefore, we will follow the study cohort prospectively to obtain incidence rates of outcomes of interest and evaluate changes in outcomes over time.

To summarize, the current literature lacks information on long-term noncancer outcomes in women at increased risk of breast/ovarian cancer who have undergone early oophorectomy. With this study, we will be able to provide insights into the prevalence and severity of CVD, osteoporosis, cognitive impairment, and HRQoL effects after RRSO. This knowledge will yield evidence-based information for women and for health care providers about the long-term effects of early RRSO. The results can be incorporated in decision-support tools about risk-reducing surgeries in *BRCA1/2* mutation carriers considering RRSO and can be used to offer individualized counseling about additional screening and interventions for noncancer diseases or complaints after RRSO.

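### The Discussion's general claim of sufficient subgroup power fails for coronary calcium and cognition in the breast cancer strata, and separate analyses there cannot show whether the RRSO effect differs

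*Protocol article*

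**What the plan says.** In the Protocol article, Statistical Analysis, the authors put the share with past breast cancer at about 40% and commit to a split on it: they "will perform the analyses separately in women with and those without a breast cancer history, as breast cancer treatment may affect outcomes". The next sentence reads "Additional subgroup analyses will be performed according to HRT use (yes/no") and goes on to BRCA1/2 status, age at RRSO (split at 40 years) and time since RRSO (split at 15 years). That makes five factors in all.

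Power is addressed in two places:
- **Sample Size Calculation.** The figures given are for the whole sample. For CAC, "with 250 women in the late/non-RRSO group and 500 women in the early RRSO group", the statement is "we have 80% power to detect an odds ratio of 1.9 at an α value of 5" percent. The section ends, directly after the HRQoL calculation, by calling the sample ample for subgroup work too.
- **Discussion, strengths.** The claim is general: "owing to the large number of participants, we will have sufficient power for subgroup analyses".

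**The concern.** A sample that gives 80% power for CAC as a whole cannot keep that power when cut in two, so the general claim looked inconsistent with the article's own calculation. If it is wrong, two errors follow. A non-significant result in one breast cancer stratum may be read as absence of harm when the stratum was simply too small. And a result that is significant in one stratum but not in the other may be read as a difference in the RRSO effect, which a pair of separate significance tests does not establish.

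**Working it through.** **Inputs (Protocol article)**
- 250 late/non-RRSO and 500 early RRSO women; CAC control rate: "10% of subjects between 55 and 65 years of age exceed this value"; hypothesised early-RRSO rate 20%; stated detectable OR 1.9 (Sample Size Calculation).
- BMD difference 0.07 with SD 0.15, i.e. 0.467 SD; cognition 0.25 SD with 90% power; HRQoL 0.5 SD (Sample Size Calculation).
- Alpha 5%. Cognition is explicitly two-sided ("value set at .05 (two tailed"). Sidedness is not stated for CAC; two-sided is assumed.
- 40% with a breast cancer history (Statistical Analysis). Assumed: the same share in both groups, so the strata are 100 vs 200 and 150 vs 300.

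**Formulas (normal approximation, unadjusted)**
- Proportions: power = Φ[(|p2 − p1| − 1.96·SE0)/SE1], with SE0 pooled and SE1 unpooled.
- Means: power = Φ[d/√(1/n1 + 1/n2) − 1.96].

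**Reproducing the article's figures**
- OR 1.9 on a 10% control rate: odds 0.1111 × 1.9 = 0.2111, so p2 = 0.1743. With 250 vs 500: SE0 = 0.0276, SE1 = 0.0255, power = Φ(0.79) = 79%, against 80% stated (one-sided would give 87%).
- Cognition: √(1/250 + 1/500) = 0.0775; 0.25/0.0775 − 1.96 = 1.27; power = 90%, as stated.

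**Power within the breast cancer strata**

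| Outcome and effect | 100 vs 200 | 150 vs 300 |
|---|---|---|
| CAC >100, OR 1.9 | 39% | 55% |
| CAC >100, 20% vs 10% | 60% | 79% |
| Cognition, 0.25 SD | 53% | 71% |
| BMD, 0.467 SD | 97% | over 99% |
| HRQoL, 0.5 SD | 98% | over 99% |

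Two examples. CAC at OR 1.9, smaller stratum: SE0 = 0.0437, SE1 = 0.0402, Φ(−0.28) = 0.39. Cognition, smaller stratum: √(1/100 + 1/200) = 0.1225; 0.25/0.1225 − 1.96 = 0.08; Φ(0.08) = 0.53.

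**Chance of a split verdict when the true effect is the same**

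The strata contain different women, so P(exactly one significant) = a(1 − b) + b(1 − a), where a and b are the two powers.
- CAC, OR 1.9: 0.390 × 0.447 + 0.553 × 0.610 = 0.51.
- CAC, 20% vs 10%: 0.601 × 0.212 + 0.788 × 0.399 = 0.44.
- Cognition: 0.532 × 0.295 + 0.705 × 0.468 = 0.49.
- BMD: 0.968 × 0.003 + 0.997 × 0.032 = 0.035 (0.04 by simulation).
- No true effect: 2 × 0.05 × 0.95 = 0.095.

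**Age at RRSO and time since RRSO.** These in effect divide only the early RRSO group, so both levels share the 250 comparators. Assuming a 50/50 split (the article gives no shares), simulation gives a split verdict in about 30% of studies at an effect with 80% overall power, 23% at 0.25 SD, and under 1% for BMD.

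**With an interaction test instead.** The false-contrast rate is 5% per factor whatever the main effect. Over five factors it is 1 − 0.95^5 = 0.226 per outcome (0.22 to 0.23 simulated). The cost is power. For cognition across the breast cancer strata, the standard error of the difference in effects is √(0.1225² + 0.1²) = 0.158. Even a true difference of 0.25 SD would then be detected with probability Φ(0.25/0.158 − 1.96) = Φ(−0.38), about 35%.

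**The case against.** The strongest reply is that this is a condensed article: interaction terms, multiplicity rules and exploratory labels usually sit in an analysis plan, which is not shown. That stands, and their absence is not held against the article here. It does not rescue the power statement, which the article makes itself and its own inputs contradict.

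A second reply is that the stated reason for the breast cancer split is that treatment may affect outcomes. That can mean control of a prognostic factor, not a search for effect modification. This is fair; separate analysis is a legitimate way to obtain stratum estimates. The problem arises only when the two results are compared by their significance.

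A third is that the closing sentence of the Sample Size Calculation may refer only to HRQoL, where the strata are large enough. That too is a fair reading. The Discussion sentence carries no such limit.

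Stronger readings are tempting, but the document does not support them:
- A reader might infer that subgroups will be tested at the full 5% and effect differences read from the p-values. No subgroup alpha and no such rule is stated.
- A reader might infer that false contrasts are about as likely as not throughout. That holds for CAC and cognition in the breast cancer split, but not for BMD, not when there is no effect, and not for the two RRSO-timing factors.
- A reader might count 30 tests (ten subgroups, three outcomes) and quote the chance of any significant result under the null, about 53% at an outcome correlation of 0.5. That is a family-wise rate resting on assumed subgroup shares. It is not the rate of false contrasts.
- A reader might take the sentence that results "can be used to offer individualized counseling about additional screening and interventions for noncancer diseases or complaints after RRSO" as advice built on subgroups. Its subject is the study's results as a whole.

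**Conclusion.** The claim of sufficient power for subgroup analyses is wrong as a general statement. In the breast cancer strata it fails for two of the three primary domains: no CAC figure and no cognition figure reaches 80% in either stratum, with a range from 39% to 79%. It holds there for BMD and for HRQoL at half an SD. For CAC at OR 1.9 and for cognition, an identical effect in both strata would give a split verdict in about half of studies (44% for CAC at 20% vs 10%), so separate analyses read by significance cannot show whether the effect differs.

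These figures assume a 40/60 split equal in both groups, full recruitment of 250 and 500, two-sided 5% tests and no covariate adjustment. Power for the other four factors cannot be fixed from the article because it gives no subgroup shares.

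**What to change.** 1. In the Discussion, limit the subgroup power claim to BMD and HRQoL in the breast cancer strata, or state the actual stratum power for CAC and cognition. Make the same change to the last sentence of the Sample Size Calculation if it is meant beyond HRQoL.
2. In Statistical Analysis, keep the stratum-specific estimates with 95% CIs, but take them from one model per primary outcome with an RRSO-group by factor interaction for breast cancer history, HRT use and BRCA status.
3. For age at RRSO and time since RRSO, use a direct contrast between the early-RRSO levels in a model that keeps the shared comparators, since a group-by-factor interaction is not defined there.
4. Claim a difference in effect only on that interaction test or contrast.

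The cost is wording and a few model terms on data already being collected. The downside is that interaction tests have low power, so fewer differences can be claimed. With one 5% test per factor, the chance of at least one false contrast over five factors is still about 23% per outcome.

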### Sample Size Calculation

We based our sample size calculations for cardiovascular status on subclinical atherosclerosis by assessing the differences in the CAC score between women in the early RRSO group and women in the late/non-RRSO group. We chose a clinically relevant cutoff for the CAC score of 100 Agatston units (AU). According to the MESA trial, 10% of subjects between 55 and 65 years of age exceed this value [78]. For sample size estimation, we hypothesized that 20% of the early RRSO group exceeds this value of 100 AU. In logistic regression with an elevated CAC score (>100) as the outcome and with 250 women in the late/non-RRSO group and 500 women in the early RRSO group, we have 80% power to detect an odds ratio of 1.9 at an α value of 5%.

With 750 women in our study, we will be able to detect a difference of 0.07 g/cm^2^ in BMD between the early RRSO and late/non-RRSO groups, as observed between women with premature and normal menopause and assuming an SD of 0.15 [79]. Statistical power for analysis of cognitive functioning is based on a previous neuropsychological study on the effects of oophorectomy on cognitive impairment and dementia [34]. This study reports relevant differences in 427 women with bilateral oophorectomy before the age of 49 years, compared to age-matched women without oophorectomy, with a median follow‐up of 25 years. As our neurocognitive tests are more sensitive than the tests screening for dementia, we expect to be able to detect smaller differences in cognitive functioning and distinguish between different cognitive domains, and with 750 participants, we have 90% power to detect an effect size of 0.25 with a *P* value set at .05 (two tailed). To detect a relevant difference between groups for the various HRQoL measures, we will use a half SD (an effect size of 0.5) to define clinically relevant group differences (over time). This requires about 67 patients per group. The available sample will be more than adequate to conduct subgroup analyses as well.

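### The general claim of sufficient subgroup power does not hold for CAC and cognition when the sample is split by breast cancer history, though it does for BMD and HRQoL

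*Protocol article*

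**What the plan says.** Sample Size Calculation bases the CAC power on an Agatston score above 100. For the reference rate it says "According to the MESA trial, 10% of subjects between 55 and 65 years of age exceed this value", and for the exposed group "we hypothesized that 20% of the early RRSO group exceeds this value of 100 AU". With "250 women in the late/non-RRSO group and 500 women in the early RRSO group" it concludes that "we have 80% power to detect an odds ratio of 1.9 at an α value of 5" per cent. For cognition it gives 90% power at an effect size of 0.25 with 750 participants, two-tailed. For BMD it says a difference of 0.07 g/cm² (SD 0.15) is detectable. For HRQoL it sets half an SD as relevant and puts the need at about 67 per group. The section then ends: "The available sample will be more than adequate to conduct subgroup analyses as well".

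Statistical Analysis first describes the early versus late/non-RRSO comparison without a split. It then expects about 40% of women to have a breast cancer history and says the authors "will perform the analyses separately in women with and those without a breast cancer history". Further subgroups follow: HRT use, mutation status, age at RRSO and time since RRSO.

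The Discussion lists as a strength that "owing to the large number of participants, we will have sufficient power for subgroup analyses". It names no outcome. The article gives no power figure for any stratum.

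**The concern.** CAC, BMD and cognition are the three areas of the primary aim. The power figures for CAC and cognition belong to the whole sample, yet the plan commits to analysing it in two parts and asserts that power remains sufficient. If that is untrue for CAC and cognition, a non-significant stratum result would be read as evidence of no effect when it may only reflect a small stratum. If one stratum is significant and the other is not, the contrast may be read as a real difference between women with and without breast cancer. The article says the results will enter follow-up guidelines and individual counselling, so either misreading would matter.

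**Working it through.** **Inputs.** From Sample Size Calculation: 250 versus 500 women; CAC above 100 in 10% of the late/non-RRSO group; odds ratio 1.9, or hypothesised rates 20% versus 10%; cognition effect size 0.25; BMD 0.07 with SD 0.15; HRQoL 0.5 SD; α 5%. From Statistical Analysis: 40% with a breast cancer history.

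**Assumptions.** The 40% is the same in both RRSO groups, so the strata are 150 versus 300 (no history) and 100 versus 200 (history). CAC testing is two-sided, as stated for cognition. There is no confounder adjustment.

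**CAC formula.** Odds ratio 1.9 from 10% gives odds 0.1111 × 1.9 = 0.2111, hence p1 = 0.2111/1.2111 = 17.43%. Power = Φ[(p1 − p0 − 1.96·SE0)/SE1]. SE0 uses the pooled proportion 14.95%, and SE1 uses the separate proportions.

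- 250 versus 500: (0.0743 − 1.96 × 0.02762)/0.02545 = 0.79, power 78.6%. The plan's 80% is reproduced.
- 150 versus 300: (0.0743 − 1.96 × 0.03566)/0.03286 = 0.13, power 55%.
- 100 versus 200: (0.0743 − 1.96 × 0.04368)/0.04024 = −0.28, power 39%.

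**Continuous outcomes.** Power = Φ[d/√(1/n0 + 1/n1) − 1.96]. The root is 0.0775 for the full sample, 0.1000 without history and 0.1225 with history. For cognition:

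- full sample: 0.25/0.0775 − 1.96 = 1.27, power 90%. The plan's 90% is reproduced.
- no history: 2.50 − 1.96 = 0.54, power 71%.
- history: 2.04 − 1.96 = 0.08, power 53%.

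For BMD, d = 0.07/0.15 = 0.467.

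| Outcome | Full sample | No history | History |
|---|---|---|---|
| CAC, odds ratio 1.9 | 79% | 55% | 39% |
| CAC, 20% versus 10% (odds ratio 2.25) | 95% | 79% | 60% |
| Cognition, 0.25 | 90% | 71% | 53% |
| BMD, 0.07 | >99.9% | 99.7% | 97% |
| HRQoL, 0.5 SD | >99.9% | 99.9% | 98% |

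**Detectable effects at 80% power.** The CAC odds ratio is about 1.92 in the full sample, 2.3 without history and 2.7 with history. For cognition, 2.80 × 0.1000 = 0.28 and 2.80 × 0.1225 = 0.34.

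**Sensitivity of the CAC figures at odds ratio 1.9.** Other two-sided formulas give 49–62% and 32–46% (75–83% in the full sample). A breast cancer share of 30–50% in the late/non-RRSO group, with 300 cases overall, gives 50–59% and 32–44%. One-sided testing gives 68% and 52%, but then the full sample would have 87%, further from the stated 80%. No variant brings either stratum to 80%.

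**Chance of discordant strata.** If the true odds ratio is 1.9 in both strata, exactly one is significant with probability 0.553 × 0.610 + 0.447 × 0.390 = 51%. For cognition at 0.25 the figure is 0.705 × 0.468 + 0.295 × 0.532 = 49%.

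**Interaction.** The log odds ratio variances are 0.0972 and 0.1459. The SE of their difference is √0.2431 = 0.493, and exp(2.80 × 0.493) = 3.98. Only a ratio of about 4 between the two odds ratios is detectable with 80% power.

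**The case against.** The adequacy sentence in Sample Size Calculation directly follows the HRQoL figure of 67 per group, and in that setting it is right: each breast cancer stratum has at least 100 women per group. BMD is also amply powered. A reader might infer that every split analysis falls short; the table shows otherwise. This part of the objection stands, and it narrows the point to CAC and cognition. It does not remove the point, because the Discussion makes the claim for subgroup analyses in general.

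Odds ratio 1.9 is below the hypothesised effect. At 20% versus 10% the stratum without breast cancer has 79% power, essentially the usual standard, so 55%/39% should not be quoted alone. The stratum with a history still has only 60%, and cognition is unaffected.

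The unsplit comparison is described first and is the one powered. A reader might take the strata to be the main analyses, but the text does not settle that; the pooled comparison is at least as natural a reading.

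Two further inferences are unsupported. One is that both strata will probably be non-significant. At the stated effects the chance is 0.447 × 0.610 = 27% for CAC and 0.295 × 0.468 = 14% for cognition. The other is that HRQoL power fails by HRT use because HRT is contraindicated after breast cancer. The article gives no HRT prevalence, a contraindication after diagnosis does not exclude earlier use, and the questionnaire records timing of use.

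**Conclusion.** The concern holds for two of the three primary outcome areas. Neither stated full-sample power figure is wrong; the error is the general statement that subgroup power is sufficient. By breast cancer history, without/with, power is about 55%/39% for CAC at odds ratio 1.9, 79%/60% at the hypothesised rates, and 71%/53% for cognition at 0.25. The statement is correct in these strata for BMD and HRQoL. The figures rest on equal breast cancer shares in both groups, 2:1 allocation within strata, a 10% control rate, two-sided 5% tests and no confounder adjustment, which the plan includes and which may change power. The practical risk is over-reading a non-significant stratum or a discordant pair of strata.

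**What to change.** - In Sample Size Calculation and the Discussion, limit the adequacy statements to BMD and HRQoL in the breast cancer strata.
- Give the stratum power for CAC at both effect sizes and for cognition, or the detectable effects (CAC odds ratios of about 2.3 and 2.7; cognition about 0.28 and 0.34), with the assumptions.
- State that the pooled 750, adjusted for breast cancer history, is the main analysis.
- Report the CAC and cognition strata and the other subgroups as estimates with confidence intervals. Judge any difference between the strata by an RRSO-by-history interaction, acknowledged to have low power, and not by significance in one stratum alone.

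The cost is wording and a less favourable power statement. No extra participants or measurements are needed.

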## Results

This study was funded by the Dutch Cancer Society in 2016. The Institutional Review Board of the Netherlands Cancer Institute approved this nationwide multicenter study in July 2018, and local approval from the participating sites followed in the months thereafter.

This study will be conducted according to the standards of Good Clinical Practice, in agreement with the principles of the Declaration of Helsinki and with the Dutch law as stated in the Medical Research Involving Human Subjects Act (WMO). The study has been approved in writing by the Medical Ethics Committee of the Antoni van Leeuwenhoek/Netherlands Cancer Institute (AVL/NKI) to be conducted in all nine University Medical Centers and the Antoni van Leeuwenhoek and has been registered at “CCMO Toetsingonline” from the Dutch Central Committee on Research involving Human Subjects (file number NL63554.031.17) and on ClinicalTrials.gov (NCT03835793). Written informed consent will be collected from the participants.

In February 2019, we included our first participant, and as of November 2020, we had enrolled 364 participants in our study. Of these 364 participants, 228 are in the early RRSO group and 136 are in the late/non-RRSO group. Recruitment of participants is currently ongoing. Results will be disseminated through peer-reviewed publications and will be incorporated in follow-up guidelines.

